## Abstract

**Background:**

Diabetes is a common disease with self-management a key aspect of care. Large prospective trials have shown that maintaining glycated hemoglobin less than 7% greatly reduces complications but translating this level of control into everyday clinical practice can be difficult. Intensive improvement programs are successful in attaining control in patients with type 2 diabetes, however, many patients experience glycemic relapse once returned to routine care. This early relapse is, in part, due to decreased adherence in self-management behaviors.

**Objective:**

This paper describes the design of the Glycemic Relapse Prevention study. The purpose of this study is to determine the optimal frequency of maintenance intervention needed to prevent glycemic relapse. The primary endpoint is glycemic relapse, which is defined as glycated hemoglobin greater than 8% and an increase of 1% from baseline.

**Methods:**

The intervention consists of telephonic contact by a nurse practitioner with a referral to a dietitian if indicated. This intervention was designed to provide early identification of self-care problems, understanding the rationale behind the self-care lapse and problem solve to find a negotiated solution. A total of 164 patients were randomized to routine care (least intensive), routine care with phone contact every three months (moderate intensity) or routine care with phone contact every month (most intensive).

**Conclusion:**

The baseline patient characteristics are similar across the treatment arms. Intervention fidelity analysis showed excellent reproducibility. This study will provide insight into the important but poorly understood area of glycemic relapse prevention.

## Background

Diabetes is a common disease and has great impact on the individual and society[1]. The burden of diabetes is expected to increase as the population ages, becomes more ethnically diverse and more obese[2]. Self-management of diabetes is critical to prevent the complications associated with diabetes and, yet, remains difficult for many patients to sustain.

Recent large randomized controlled trials have proven that tight glycemic control reduces the microvascular and macrovascular complications of diabetes [3-5]. Reduction of these complications also leads to a great cost savings to healthcare and society[6]. However, it has been difficult to translate the success of these large randomized control trials to everyday practice [7-9]. A recent cross-sectional analysis of 95 clinicians revealed only 40.5% of type 2 diabetes patients had a glycated hemoglobin (HbA1c) less than 7%[9]. Even large, well-conducted, multi-factorial randomized controlled trials aimed at reducing HbA1c have not had success in maintaining long-term glycemic control[10]. The disparity of care between the large trials and a primary care office is largely due to the difference in resources available in the typical medical office. Practical, sustainable ways of maintaining tight glycemic control are needed in everyday practice. Indeed, a number of for profit corporations have entered this arena of disease management given a seeming inability of the current clinical milieu to adequately address this issue.

While diabetes improvement programs are successful in acutely lowering HbA1c [11-24] the long-term effectiveness of these programs is disappointing. Approximately 40% of those who return to routine care after completing an intensive diabetes improvement program experience a relapse in their glycemic control within one year [25-27]. While some of the glycemic relapse may represent a natural progression of the underlying disease, it is unlikely that such a high percentage would experience such significant disease progression in such a short period of time[4,28]. Some proportion of the relapse is likely due to a patient's inability to maintain adherence to key self-care behaviors – diet, exercise, self-monitoring of blood glucose and medication regimen. Little is known about the optimal frequency, intensity or nature of maintenance interventions needed to prevent deterioration of self-care behaviors that lead to glycemic relapse.

## Hypothesis

The purpose of this study is to better understand prevention of glycemic relapse. The primary aim of this study is to assess the relative effectiveness of three management approaches, varying in frequency, for preventing glycemic relapse after glycemic control has been achieved through participation in an intensive diabetes improvement program. This study will determine the optimal frequency of intervention needed to prevent glycemic relapse in patients with type 2 diabetes. The authors hypothesize that high intensity intervention will lead to a decrease in glycemic relapse in a dose dependent fashion.

Other aims to be addressed in this study include determination of patient characteristics and behaviors predictive of glycemic relapse. In doing so, specific subgroups in need of alternative maintenance strategies will also be identified. Finally, this study will also determine the differences in activity cost between the intervention arms using activity based accounting.

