### Study size

Sample size calculation was performed based on chi-square test for linear trend in proportions of patients among the three study arms who relapsed during the study period (118). We expected 50% of patients who are assigned to study arm A (routine primary care follow-up) relapse during the study period, 30% in the study arm B (scheduled 3 month interaction with a certified nurse), and 20% in the study arm C (scheduled 1 month interaction with a certified nurse). Anticipating 20% attrition, 165 subjects (55 recruited/44 complete study) will provide 85% power to detect statistically significant linear trend at 2-sided 5% alpha level. Calculations for power analysis were performed by using nQuery Advisor version 4.0 (Statistical Solutions, Stonehill Corporate Center, Saugus, MA).

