Limitations of this study include reproducibility of the intervention and the possible differences in the routine care received. While the intervention is outlined in this article, it may be difficult to reproduce the problem solving skills used by the nurse practitioners in this study for someone with no prior training. The frequency of the intervention is varied but not the intervention content – it is possible that another intervention would be more effective. This study was not designed to compare effectiveness of different interventions, but to determine the optimal frequency of an intervention that was thought to be optimal based on a previously published meta-analysis[41]. The study protocol did not address how often the subjects saw their primary care providers, the care provided by the primary care providers or counseling given in that setting.

This study seeks to assess the efficacy of varying frequencies of a highly structured nurse initiated telephonic intervention for the prevention of glycemic relapse. Prevention of glycemic relapse is a novel area in diabetes care that remains largely unstudied. By adjusting the frequency of the intervention, the optimal "dose" of intervention to maintain adequate glycemic control can be determined. This study will add to the fund of knowledge on longitudinal diabetes care.

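### The aim promises the optimal contact frequency, but the linear trend the trial is sized on supports a dose-response conclusion and does not identify that frequency

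*Protocol article*

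**What the plan says.** The Hypothesis section of the protocol article makes two claims. One is an aim: "This study will determine the optimal frequency of intervention needed to prevent glycemic relapse in patients with type 2 diabetes". The other is a directional hypothesis: "The authors hypothesize that high intensity intervention will lead to a decrease in glycemic relapse in a dose dependent fashion". The last paragraph of the Discussion returns to the aim: "By adjusting the frequency of the intervention, the optimal" dose "of intervention to maintain adequate glycemic control can be determined".

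The Study size section names one test: "Sample size calculation was performed based on chi-square test for linear trend in proportions of patients among the three study arms who relapsed". Its assumptions are 50% relapse under routine care (arm A), 30% with quarterly calls (arm B) and 20% with monthly calls (arm C). It plans 55 recruited and 44 completing per arm after 20% attrition, and states 85% power at a two-sided 5% level. The scores given to the arms are not stated. The article states no arm-versus-arm comparison and no rule for choosing a frequency.

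**The concern.** A dose-dependent fall in relapse and an optimal frequency are different targets. The first needs evidence that relapse declines across ordered arms. The second needs evidence on each step: whether quarterly calls beat routine care, and whether monthly calls beat quarterly calls. The stated test gives one p-value that hardly depends on where the quarterly arm lies between the other two.

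Table 1 gives 24 contacts in the monthly arm and 8 in the quarterly arm, so monthly contact takes three times as many calls. The Discussion wants the results to inform chronic care services on efficacy and cost-effectiveness. If a significant trend were read as showing that monthly contact is optimal, the extra 16 calls per patient could be adopted on evidence that does not separate the two schedules.

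**Working it through.** **Inputs.** Rates pA = 0.50, pB = 0.30, pC = 0.20; n = 44 completers per arm; two-sided 5%, z = 1.96 (all from Study size). Equally spaced scores 0, 1, 2 are an assumption, tested in steps 1 and 2.

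**1. Reproducing the stated power.** The trend (Cochran-Armitage) statistic has numerator T = Σ n·p·(x − x̄). Its null variance is V0 = p̄(1 − p̄)·Σ n(x − x̄)², and its variance under the alternative is V1 = Σ n·p(1 − p)(x − x̄)².

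- Centred scores are −1, 0, +1, so |T| = 44 × (0.50 − 0.20) = 13.2.
- p̄ = 1/3, so V0 = (1/3)(2/3) × 88 = 19.56, square root 4.422.
- V1 = 44 × (0.25 + 0.16) = 18.04, square root 4.247.
- Power = Φ[(13.2 − 1.96 × 4.422)/4.247] = Φ(1.067) = 85.7%.

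The smallest n per arm giving 85% is 44, and 44/0.80 = 55 recruited per arm, 165 in all. The stated figures reproduce. Scores set to the number of calls (0, 8, 24, taking control as 0) give 82.1%, a poorer match.

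**2. Weight of the quarterly arm.** With equal arms its centred score is 0, so pB drops out of T and enters only through p̄ in V0. With the achieved 54/55/55 allocation (Population characteristics), x̄ = (55 + 110)/164 = 1.006, so the weight is −0.006. With scores 0, 8, 24 the centred weights are −10.7, −2.7 and +13.3: small for the quarterly arm, but not zero.

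**3. Changing only the quarterly rate** (A = 50%, C = 20%, so T and V1 stay the same):

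| Quarterly rate | Meaning | p̄ | √V0 | Trend power |
|---|---|---|---|---|
| 20% | as good as monthly | 0.300 | 4.299 | 87.0% |
| 30% | planned | 0.333 | 4.422 | 85.7% |
| 50% | no better than routine care | 0.400 | 4.596 | 83.8% |

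**4. Pairwise power at the planned rates.** Power = Φ[(|d| − 1.96·s0)/s1], with s0 the pooled and s1 the unpooled standard error at 44 per arm, unadjusted for multiplicity.

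- B v C, 30% v 20%: s0 = 0.0923, s1 = 0.0917; Φ(−0.883) = 18.9%.
- A v B, 50% v 30%: s0 = 0.1044, s1 = 0.1022; Φ(−0.046) = 48.2%.
- A v C, 50% v 20%: s0 = 0.1017, s1 = 0.0965; Φ(1.043) = 85.2%, almost the power of the trend test itself.

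The 95% interval half-width for B v C is 1.96 × √[(0.21 + 0.16)/44] = 0.180, or 18 points around an expected difference of 10. By the same method, 85% power for B v C needs 336 completers per arm. With no attrition at all (55 per arm) its power is 22.5%.

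**5. Possible gates for formal pairwise tests** (simulation, 44 per arm; share of trials in which the gate opens):

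| True rates A/B/C | Trend gate | 2-df global chi-square gate |
|---|---|---|
| 50/30/20 (planned) | about 86% | about 79% |
| 50/20/40 (quarterly best) | about 18% | about 79% |

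Under 50/20/40, A v B is significant in about 86% of trials without a gate and in about 17% behind the trend gate.

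**The case against.** Four points can be made for the plan.

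- **The trend test suits the stated hypothesis.** A one-degree-of-freedom trend test is standard for an ordered alternative, and the sample size is right. This stands: neither the test nor the number of patients is wrong.
- **This is a design article.** Pairwise contrasts and multiplicity rules are commonly left to a full protocol or analysis plan. A reader might infer that no arm-versus-arm comparison is planned; the document supports only that none is stated here. The mismatch remains, because no analysis plan could lift the 30% v 20% comparison much above 19% power with these numbers.
- **The arm rates will be visible, and some scenarios are well powered.** A reader might infer that the trial can say nothing about frequency. That goes too far. If quarterly calls are useless (50/50/20), B v C has about 86% power; if they equal monthly calls (50/20/20), A v B has about 86%. Power is lacking for the intermediate gradient, which is the one the authors expect.
- **The zero weight depends on equal spacing.** The scores are not stated. Equal spacing is an inference from the reproduced 85%. Call-count scores would give the quarterly arm a small weight and leave B v C power unchanged.

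**Conclusion.** The concern holds as a mismatch between the stated aim and the test that was sized. A significant trend would support lower relapse with more frequent contact. It would not show which frequency is best, because it arises with 84% to 87% probability across quarterly rates that imply opposite answers. At the planned rates, power is about 19% for quarterly v monthly and about 48% for control v quarterly.

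This rests on equally spaced scores, near-equal arms, 44 completers per arm and the article's assumed rates. The pairwise figures do not depend on the scores. It is a should-fix: the data and the main test stay as they are, but what the trial may conclude changes.

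**What to change.** 1. Keep the linear trend as the primary test of the dose-dependent hypothesis, and state its scores.
2. In the Hypothesis section and the last paragraph of the Discussion, restate the aim as whether relapse falls as contact frequency rises, with estimates of each step.
3. Report all three pairwise risk differences with 95% confidence intervals, whether or not the trend is significant.
4. State that at the planned rates the trial has only about 19% power to separate quarterly from monthly contact, and that a significant trend does not show monthly contact to be optimal.
5. If formal pairwise tests are wanted, do not gate them on the trend test, because that gate rarely opens if quarterly calls are best. A 2-df global chi-square gate followed by each pairwise test at 5% is a closed procedure with three arms, so familywise error is held at 5%.

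The cost is revised wording and three reported differences, with no new data or patients. Enrolment has closed at 164, so adding patients is not a practical remedy. If the optional gate is used, it opens in about 79% of trials at the planned rates, against about 86% for the trend; the primary trend test loses nothing.

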## Methods

### Study Design

This study is a prospective, randomized control trial to assess the relative effectiveness of three management strategies for the purpose of preventing glycemic relapse in type 2 diabetes. The subjects will be randomized to one of three arms: routine follow-up in a primary care clinic (control), telephone contact every three months (moderate intensity) or telephone contact every month (high intensity). The duration of the study is 24 months. At the completion of the intervention period, the subjects will be asked to complete another 12 months of follow-up during which everyone will receive routine care only. The primary endpoint is glycemic relapse. Glycemic relapse is defined as a HbA1c greater than 8% and an increase by 1% point from baseline. The primary analysis will be based on intention to treat.

### Study Setting

Telephonic intervention based out of an academic center in middle Tennessee. At recruitment, study participants lived in the city and surrounding suburbs of the academic center.

### Study Population

All subjects are recruited after completion of a 12 week outpatient, intensive diabetes improvement program following referral for poor glycemic control (HbA1c>8%). The intensive improvement program consists of instruction and support in diabetes self-management coupled with intensification of glycemic medications, including insulin. It is provided by nurse practitioners and supervised by a practicing diabetologist. The educational content includes diet, exercise, self-monitoring of blood glucose and medication adherence as well as instruction in preventive measures such as foot care and screening for complications. Upon completion of the program, only those subjects referred to the improvement program for poor glycemic control (HbA1c>8%) and who obtained control (HbA1c<8% and at least an absolute 1% decline in HbA1c) during the program were recruited. Only subjects aged 18–75 years of age were included. Pregnant women were excluded.

### Randomization

Two weeks after completion of the improvement program, a research assistant contacted patients and gave them a brief explanation of the study. The subjects were then invited to participate in the study if they met the defined inclusion criteria. A research assistant confirmed eligibility. After informed consent was obtained, patients were randomly assigned to one of three study arms. Randomization applied permuted block scheme for balancing interval, varying randomly among 3, 6, 9 and12 according to the outcome of a computer generated random number. This ensured that the cumulative number of assignments to each treatment would be in balance after each block of assignments had been made. The allocation sequence was written by the statistician involved with the trial. Once treatment arm status was assigned by the research assistant, subjects in the intervention arms were assigned a study nurse practitioner. Due to the nature of this intervention, blinding of participants, investigators and study nurse practitioners was not possible. See Figure 1 for enrollment and randomization scheme.

### Intervention

The intervention consists of a phone contact by a nurse practitioner with a referral to a dietitian if nutrition self-care is perturbed. The characteristics of the intervention are described in Table 1 using a diabetes intervention taxonomy previously characterized[29] The duration of each contact was monitored. During the first session, shared goal setting was established and referred to or modified during subsequent contacts. The method and content of the phone contacts varied based on the assessment. If there were no problems related to glycemic control or self-care behaviors identified, then Protocol 1 was followed (see Figure 2). If a problem was identified, Protocol 2 was followed (see Figure 2). The intervention does not vary between the treatment arms; only the frequency of the intervention varies.

**Table 1 T1:** Intervention Structure

Setting	One-on-One
Delivery	Phone contact
Teaching Methods	Shared goal setting Problem solving Cognitive re-framing Diaries
Content	Diet Exercise Self-monitoring of blood glucose Medication management
Provider	Diabetes certified nurse educator with a dietician referral if diet self-care is perturbed
Tailoring of intervention to an assessment	Yes
Modification of intervention with follow-up	Yes
Intensity of intervention	
Number of episodes	Arm 2: 8 Arm 3: 24
Duration of episodes	Measured as part of study protocol
Duration of study	24 months
Initial supplement given	No

**Figure 1 F1:**
[figure not shown]
Enrollment and Randomization.

**Figure 2 F2:**
[figure not shown]
Telephone Contact Intervention Flow Sheet.

Protocol 1 is characterized by anticipatory planning for potential lapses, including practicing a coping skill, and also offers self-efficacy enhancement through positive reinforcement, short-term goal setting and cognitive rewards. If a self-care problem was identified then protocol 2 was followed. The subject was asked to identify the source of the struggle. If readily identified, the interviewer employed a 5 step problem solving paradigm: 1) Define problem clearly, 2) Brainstorm strategies, 3) Choose a strategy, 4) Develop an action plan and 5) Try it and revise as needed. If a subject was unable to identify a reason for deteriorating self-care behavior, motivational interviewing was employed largely as a diagnostic modality[30] Subjects were asked to assess the importance of and their confidence in correcting the lapse behavior. The individual was then asked to comment on what prevented them from giving a higher importance/confidence score. This often identified an underlying problem which led back to the problem solving paradigm. In addition to providing a diagnostic tool for identification of the reasons behind the lapse, the motivational interview may also provide a cue to action via the subject's reflection during the assessment.

The interviewer worked with the subject to correct (e.g. correcting a cognitive distortion) the underlying reason for the perturbation of the self-care behavior. If the obstacle could not be corrected (i.e. divorce, financial barrier), then the interviewer worked with the subject to develop a coping mechanism. However, if the subject remained unable to identify a reason for lapse in self-care behavior or to devise a coping strategy, the interviewer worked with the subject to negotiate a change in another self-care behavior as a compensation for the perturbed behavior. A negotiated compensation, for example, may include increased exercise, increased monitoring or increased insulin use for a perturbation of diet self-care.

### Intervention Fidelity

To enhance the reliability and validity of the behavioral intervention portion of this study, intervention fidelity tools were used to monitor the phone contacts between the nurse practitioners and the study subjects [31-33]. The analysis consisted of qualitative descriptions of the extent to which a sample of intervention phone calls was consistent with the intervention protocol (Figure 2) and guidelines. Consistency between the nurse practitioners was also determined. Raters used checklists derived from the protocols to document which elements were conducted or omitted. Overall, adherence to the protocol was quite high with almost all elements present in more than 80% of all interviews. The educators did not differ significantly in any category.

### Primary Outcome

The primary outcome is the glycemic relapse rate at 24 months. Relapse is defined as a HbA1c greater than 8% and an absolute 1% increase from baseline. The HbA1c will be measured at baseline and at 6-month intervals throughout the study.

### Secondary Outcomes

#### Activity Assessment

A pager-sized (2.8 × 2.2 × 1.1 inches, weighing 2.3 oz) triaxial portable accelerometer (RT3 Research Activity Tracker by StayHealthy, Inc. Monrovia CA) is used to measure detailed movements in the center of body mass (worn at the hip). The RT3 monitor is programmed with each study participant's weight, height, age, and gender prior to application. During each of the visits, each subject is fitted with the RT3 monitor securely on his/her right hip, either by direct clipping to the belt or using a small pouch-bag (for women who do not usually wear a waist belt). Subjects are instructed to wear the RT3 monitor during all possible non-sleeping activities, except during water sports, for the next 7 days. Once the monitor is initialized, it runs continuously without interruption from the subject (no buttons to push). At the end of the 7-day monitoring period, the RT3 is mailed back to the study coordinator via a pre-addressed/stamped bubble envelope and its data downloaded. Using the raw activity counts and a prediction model which was previously developed and validated[34], the total energy expenditure and overall physical activity levels during each study period are obtained for each subject. Furthermore, utilizing durations of activities within certain intensity categories (utilizing the minute-to-minute measurements), subject's adherence to exercise will be validated.

